## Abstract

**Background:**

Around one-third of workdays lost in Norway are due to musculoskeletal conditions, with persistent (chronic) pain being the most frequent cause of sick leave and work disability. Increasing work participation for people with persistent pain improves their health, quality of life, and well-being and reduces poverty; however, it is not clear how to best help unemployed people who have persistent pain to return to work. The aim of this study is to examine if a matched work placement intervention featuring case manager support and work-focused healthcare improves return to work rates and quality of life for unemployed people in Norway with persistent pain who want to work.

**Methods:**

We will use a cohort randomised controlled approach to test the effectiveness and cost-effectiveness of a matched work placement intervention featuring case manager support and work-focused healthcare compared to those receiving usual care in the cohort alone. We will recruit people aged 18–64, who have been out of work for at least 1 month, had pain for more than 3 months, and want to work. Initially, all (*n* = 228) will be recruited to an observational cohort study on the impact of being unemployed with persistent pain. We will then randomly select one in three to be offered the intervention. The primary outcome of sustained return to work will be measured using registry and self-reported data, while secondary outcomes include self-reported levels of health-related quality of life and physical and mental health. Outcomes will be measured at baseline and 3, 6, and 12 months post-randomisation. We will run a process evaluation parallel to the intervention exploring implementation, continuity of the intervention, reasons for participating, declining participation, and mechanisms behind cases of sustained return to work. An economic evaluation of the trial process will also be conducted.

**Discussion:**

The ReISE intervention is designed to increase work participation for people with persistent pain. The intervention has the potential to improve work ability by collaboratively navigating obstacles to working. If successful, the intervention may be a viable option for helping people in this population.

**Trial registration:**

ISRCTN Registry 85,437,524 Registered on 30 March 2022.

**Supplementary Information:**

The online version contains supplementary material available at 10.1186/s13063-023-07211-5.

Role of sponsor {5c}	The sponsor played no part in the study design and will play no part in the collection, management, analysis, and interpretation of the data; writing of the report; and the decision to submit the report for publication The sponsor has the overall responsibility for effective arrangements to be in place to set up and run the trial and provide regulatory advice as well as act as the legal signatory

## Introduction

### Background and rationale {6a}

Persistent (chronic) pain is the most frequent cause of sick leave and work disability in Norway; accounting for 11% and 9% of employed workers, respectively [1]. Most chronic pain is of musculoskeletal origin [2]. In 2019, around one-third of work days lost in Norway were due to musculoskeletal conditions [3]. Increasing work participation in sick and disabled populations improves health outcomes, reverses adverse effects of worklessness, reduces poverty, and improves quality of life and well-being [4]. In 2016, the costs of musculoskeletal conditions to the Norwegian health service were NOK 18 billion, and the total socio-economic costs were estimated to be NOK 255 billion [5]. Disability benefits increased between 2011 and 2020, and the percentage of people outside the labour market increased between 2018 and 2020 (in both cases by around 1.5%) [6, 7]. The average age of people reporting persistent pain in Norway is 48 (SD = 16) [8]. However, these people may have many remaining working years to contribute [9].

It is not clear how to best help unemployed people with persistent pain return to work (RTW). In Norway, usual care for people with persistent pain is interdisciplinary, featuring pain management services supported by physicians, psychologists, physiotherapists, and nurses [10]. Employment services in Norway take an individualised approach, often including assessments of work ability, training, and vocational rehabilitation programmes involving traineeships in sheltered businesses [11]. However, these services are not specifically tailored for people with pain. Effective vocational rehabilitation requires a combination of work-focused healthcare and supportive workplaces; unfortunately, the two are generally not coordinated [12]. Without intervention, return to work is unlikely after 2 years of unemployment [13]. Return to work rates for traditional vocational rehabilitation in the unemployed (rather than sick-listed) pain population are unclear. In 2020, we described the results of a feasibility study, done in the English Midlands, of an adapted supported work placement intervention, which featured work placement provision with case management support [13]. In this study, case managers were trained to act as a bridge between systems and institutions (e.g. between health care providers and the workplace), engage people about obstacles to work, and collaboratively agree on a return-to-work plan. We also provided supportive work placements. The developed intervention was acceptable and valued by the people involved, with around 20% of the sample obtaining paid employment within the short 6-month follow-up. The study suggested that self-perception of satisfactory functioning in role as well as management of identified obstacles may be key to increasing confidence for this group. As the study focused on feasibility, the effectiveness and cost-effectiveness of the intervention are still unknown.

### Objectives {7}

The primary objective of this study is to establish whether a supported work placement intervention with biopsychosocial case management is more effective and cost-effective than usual care for improving sustained return to work in unemployed people with persistent pain who want to work.

The secondary objectives include the following:To investigate the impact of being unemployed with persistent pain on health-related quality of life, including physical function, anxiety, depression, fatigue, sleep disturbance, social function and activities, pain interference, bothersomeness, pain intensity, mental well-being, and confidence in return to work and use of social care resourcesTo define usual care and explore what type of existing services this population typically receiveTo investigate the influence of demographics on enrolling on the cohort studyTo explore the mechanisms of action in people who achieve sustained return to work and identify possible predictive factors of sustained return to workTo describe the delivered processes in terms of fidelity, context, reach, dose, and adherence and the implementation of the intervention.

### Trial design {8}

We will use a single-site cohort randomised approach. The trial will be conducted within a superiority framework. Initially, all eligible and consenting participants will be recruited for an observational cohort study. After baseline measurement, we will randomly select one in three, to whom we will offer the intervention and request consent for intervention participation. Figure 1 illustrates the plan for the delivery of the intervention using a cascade diagram [14]. Assessments will be made at baseline and at 3-, 6-, and 12-month follow-up, and the primary outcome of return to work will be obtained from questionnaire and registry data at these time points. We will also use registry data at all follow-up time points to estimate hospital and community health and social care use for our economic analysis from a personal social services perspective. A pre-pilot informs logistical processes and pre-pilot participants may be included in the main trial if there are no substantial protocol amendments during the pre-pilot, or as a result of piloting (i.e. no alteration in the cohort and intervention delivery). Parallel to the intervention, we will run a process evaluation exploring implementation, continuity of the provided package, reasons for participating and declining participation, and mechanisms behind cases of sustained return to work. The study will be reported following the CONSORT guideline (Consolidated Standards of Reporting Trials; http://www.consort-statement.org/) extension for the reporting of randomised controlled trials conducted using cohorts and routinely collected data (Fig. 2) [15]. The study protocol has been written using the structured protocol template for Standard Protocol Items: Recommendations for Interventional Trials (SPIRIT) Checklist for intervention trials [16].

**Fig. 1 Fig1:**
[figure not shown]
Cascade diagram showing the intervention delivery

**Fig. 2 Fig2:**
[figure not shown]
CONSORT guideline extension for reporting randomised controlled trials conducted using cohorts and routinely collected data

## Methods: participants, intervention, and outcomes

### Study setting {9}

Following the exploration of remote case management support and work familiarisation by video-link in the pre-pilot, we aim to recruit nationally for the main trial. However, we anticipate most recruitment will be in the Oslo area. Placements will be sought in diverse areas including administration, warehouse, transport, media and marketing, IT, sales and service, finance, accounting, and payroll, in line with participant preference and skill.

### Eligibility criteria {10}

We will include people aged 18–64 who have been unemployed for at least 1 month, have had pain for more than 3 months, and who want to work. We will exclude those aged 65 or over as their future time in work is likely to be limited. We will exclude people who do not have sufficient Norwegian or English language skills to give consent. This criterion is in line with the fluency required to enter the open labour market in Norway.

### Who will take informed consent? {26a}

We will use online and offline recruitment channels (see SPIRIT item 15 for further details). Participants will be given a participant information leaflet describing essential information about the study. Potential participants will reply to an ‘expression of interest’ form, including self-reporting of eligibility. Additionally, contact information for the research team will be provided within the participant information leaflet and expression of interest, encouraging to make contact if they have questions. Based on preferences, the consent form will be delivered by post or through Nettskjema (UiO, Oslo) for those engaging online. Before providing consent, potential participants must confirm that they have read and understood the participant information leaflet. After receiving the consent form, a trial working group member will phone participants to confirm eligibility before inviting the participant to complete a baseline questionnaire. After completing the baseline questionnaire, one-in-three people will be randomly selected to be offered the intervention. The initial cohort study consent form will request consent to be approached for the intervention. A member from the trial working group will contact those selected by phone, providing information and to ask if they have any questions and if they might like to participate. An email or post package, based on their previous preferences, will be sent to those interested after the call, and contain a participant information leaflet describing the intervention and a consent form. If there is no response to the phone call, the email or post package will note that a member from the trial working group will contact by phone to ask if the participant has any questions or requires further information. The participant information materials and informed consent form are available from the corresponding author on request.

### Additional consent provisions for collection and use of participant data and biological specimens {26b}

The study does not collect biological data or specimens.

### Interventions

#### Explanation for the choice of comparators {6b}

In line with the pragmatic trial design, the study protocol will not restrict access to usual care [17]. Usual care for people with persistent pain is interdisciplinary in Norway, featuring pain management services supported by physicians, psychologists, physiotherapists, and nurses [10]. In general, employment services take an individualised approach, including work ability assessments, training, and vocational rehabilitation programmes involving traineeships in sheltered businesses [11]. A secondary objective of the trial is to explore what existing employment services this specific population typically receives as usual care.

#### Intervention description {11a}

First, we will train two to four people with prior experience of working with pain patients (e.g. nursing, manual/occupational therapy, or psychology) to function as case managers for participants and identify obstacles to return to work using the ‘Psychosocial Flags Framework’ and a set of stem questions [13, 18]. Using a biopsychosocial approach, the case managers will identify and create a plan to tackle obstacles across personal, workplace, and social domains, documenting these in a return-to-work plan. Case managers will receive training on how to do this using a toolkit used as the evidence base for case management and for conducting work familiarisation sessions. Case managers will also receive training on pain management strategies and the Norwegian benefits system, as they will be unaffiliated with the Norwegian Labour and Welfare Administration (NAV), which our user input suggests may be important.

The trained case manager will contact participants by phone to make an initial assessment, explore work aspirations and skills, and help the participant to identify work obstacles. A face-to-face or video will be offered if the case manager considers one needed. Through collaboration with Manpower, a large recruitment company in Norway, the case manager will match the participant with a placement, based on skills, aspirations, and suitability. From their network of associates, Manpower will provide 6-week part-time work placements of up to 16 h per week (as participants receiving work assessment allowance (*Arbeidsavklaringspenger*) may have limits on how much they are allowed to work). Once a placement is arranged, the case manager, the participant, and the placement manager will meet to agree on a return-to-work plan and discuss whether any work accommodations are needed to overcome identified obstacles to returning to work [19, 20]. While Manpower aims to provide all of our placements, we may approach additional placement providers if needed.

Our support model features a work-familiarisation session to help embed the person into their role and discuss work-focused pain management. The session will be run in small groups over 2 days by one or two facilitators in required geographic locations and by video link when outside of Oslo. The case manager will then provide regular telephone or video support to the participant and placement manager, which is known to be effective [21]. If needed, the case manager may suggest referrals to existing health services, such as cognitive behavioural therapy and physiotherapy [12]. The case manager will also aid clinicians in providing work-focused healthcare by providing existing evidence-based resources. Similar materials are given to all participants and placement providers and include culturally translated versions of (1) *advising patients about work*, (2) *health and work*, and (3) *work and health* originally commissioned to support the UK government work ability initiatives [22–24]. These will be available in Norwegian and English, following the success of offering these languages in a trial of motivational interviewing that is being conducted for people sick-listed with pain in Norway [25]. A paper on the cultural adaptation of these materials will be reported elsewhere.

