### Sample size {14}

The sample size calculation is based on detecting a difference of 20% between the intervention group and the remaining cohort achieving a sustained return to work (1:3 allocation ratio). Assuming a cohort return to work rate as high as 10%, with a power of 80% and a 5% significance level, we will need data on 176 participants (132 control and 44 intervention) [13]. Allowing for a 20% loss to follow-up and a crude 14% inflation in the intervention group for an estimated design effect due to clustering by the case manager (assumptions here are an ICC of 0.01, smallest cluster size of 7 and largest of 16, and so a design effect of 1.14), we will aim to recruit 228 people [59]. If a 1:3 ratio allocation provides insufficient throughput for us to regularly form small groups of people for the work preparation session due to the proportion of people not accepting the intervention being high, we may switch to target overall balanced randomisation (1:2). In this case, our overall required sample size will be reduced to 190 in total, with the above inflations (with the same assumptions the estimated design effect will be 1.11 in this case) [59].

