### Statistical methods

#### Statistical methods for primary and secondary outcomes {20a}

A detailed statistical analysis plan has been finalised and agreed prior to analysis by the research team. We will report all participant flow in line with the CONSORT guideline extension for reporting RCTs conducted using cohorts and routinely collected data showing withdrawal and loss to follow-up [15]. Analyses will be conducted within TSD using Stata v17 or above (Stata Corporation, College Station, TX). Participant characteristics and outcomes will be summarised as mean and standard deviation for normally distributed continuous data or with median and ranges for data with skewed distributions or counts and percentage for categorical data. The primary analysis approach will be ‘intention-to-treat’. To account for the trial design featuring clustering in the intervention arm, generalised linear (GLM) mixed effects models will be used to estimate the between-group differences for both primary and secondary continuous outcomes, adjusting for age, gender, and duration of pain, with a random intercept for case manager. For example, we will analyse the between-group differences in sustained return to work (a binary outcome) using a generalised mixed-effect model with logit link function, the above covariates, and fitting a random effect in case manager allocation.

Secondary outcomes will also be analysed using generalised mixed models, using link functions appropriate to the outcome (e.g. where outcomes are continuous, we will use a canonical link function). In all cases, we will adjust for the same covariates (i.e. age, gender, and duration of pain). The adjusted treatment effect estimates (mean difference) between the groups will be presented as point estimates within a 95% confidence interval. Our outcome measures are largely independent and no correction for multiple testing will be done. *P*-values < 0.05 will be considered statistically significant. All tests will be two-sided.

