### Harms

The frequency and percentage (%) of serious adverse events and adverse events in the trial will be compared between the two treatments using the chi-squared test provided the expected values in the cross-tabulation are greater than 5; otherwise, Fisher’s exact test will be used. Odds ratios and 95% confidence intervals will be reported. Adjusted analyses will not be performed for any harm data. The event type, severity assessment, expectedness, and relatedness to intervention will also be summarised by offer of treatment or cohort only.

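### The familiarisation session is taught in small groups, but the sample size and the primary and secondary outcome models allow for clustering by case manager only, so intervention-arm standard errors may be too small

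*Protocol article*

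**What the plan says.** - **Intervention description {11a}.** Intervention participants attend a familiarisation session, which also deals with managing pain at work: "The session will be run in small groups over 2 days by one or two facilitators". Sessions are held where they are needed, or by video link outside Oslo.
- **Sample size {14}.** Filling these groups matters enough that the allocation ratio may be changed if there is "insufficient throughput for us to regularly form small groups of people for the work preparation session". The same paragraph inflates for one source of clustering: "a crude 14% inflation in the intervention group for an estimated design effect due to clustering by the case manager". Its basis is given as "assumptions here are an ICC of 0.01, smallest cluster size of 7 and largest of 16, and so a design effect of 1.14".
- **Statistical methods {20a}.** The models are meant to account for clustering in the intervention arm. They are specified as "adjusting for age, gender, and duration of pain, with a random intercept for case manager", and for the binary primary outcome as "fitting a random effect in case manager allocation".

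No section gives a session group size, a session ICC or a session term.

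**The concern.** The protocol describes two ways in which intervention participants share delivery: a common case manager and a common session. It allows for the first only. People in one session share facilitators, place or video mode, calendar time and each other's company. If that makes their outcomes alike, they carry less information than the same number of independent people.

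The case-manager intercept does not fully cover this. With two to four case managers it describes differences between case-manager averages. Differences between sessions attended by people of the same case manager remain in the residual, where they are treated as independent.

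The affected arm is the smaller one and dominates the variance of the comparison. At 30% v 10% with 46 and 137 analysed (80% of 228, split about 1:3), the two terms are 0.21/46 = 0.00457 and 0.09/137 = 0.00066, so the intervention arm contributes 0.00457/0.00523 = 87%. At stake are the width of the confidence intervals, the type I error and the stated power.

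This is not simply detail left to the analysis plan, because the protocol itself states the clustering structure in both {14} and {20a}.

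**Working it through.** **1. Reproducing the plan's figures.** Inputs from {14} and {20a}: 10% v 30%, three controls per intervention participant, two-sided 5%, 80% power. With r = 3, d = 0.20 and pooled proportion (0.30 + 3×0.10)/4 = 0.15:

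n′ = [1.96√(4×0.15×0.85) + 0.8416√(3×0.21 + 0.09)]² / (3×0.04) = 37.2

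Continuity correction: n = (n′/4)[1 + √(1 + 2(r+1)/(n′rd))]² = 43.6, so 44 intervention and 132 control, 176 in all. Inflation: (132 + 44×1.14)/0.80 = 227.7, so 228. Both figures match the protocol.

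**2. Adding a session term.** Let g be the group size and ρ the session ICC beyond case manager. Both are assumptions. Intervention-arm design effect: DE = 1.14 + (g − 1)ρ. Recruitment target: N = (132 + 44×DE)/0.80.

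Power is for 132 control and 44×1.14 = 50.16 intervention participants analysed, with effective intervention size m = 50.16/DE and r = 132/m. It is given by the formula behind 176 (undoing the correction by n′ = m[1 − (r+1)/(2mrd)]²) and by the same formula without the correction.

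| g, ρ | DE | N | Power, formula behind 176 | Power, no correction |
|---|---|---|---|---|
| no session term | 1.14 | 228 | 80% | 85.5% |
| 5, 0.01 | 1.18 | 230 | 79% | 85% |
| 5, 0.05 | 1.34 | 239 | 76% | 82% |
| 8, 0.10 | 1.84 | 267 | 66% | 74% |

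Third row worked: m = 50.16/1.34 = 37.43 and r = 3.526. Then n′ = 37.43×(1 − 0.0857)² = 31.29, and z = [√(31.29×3.526×0.04) − 1.96√(4.526×0.1442×0.8558)]/√(3.526×0.21 + 0.09) = (2.101 − 1.465)/0.911 = 0.698, which is 76%.

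For g from 3 to 8, N is 229–232 at ρ = 0.01, 234–247 at 0.05 and 239–267 at 0.10.

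**3. Standard error of the risk difference.** The ratio to the planned value is √[(0.21×DE/50.16 + 0.09/132)/(0.21×1.14/50.16 + 0.09/132)]. At DE 1.18 it is √(0.005622/0.005455), a rise of 1.5%. At DE 1.34 it is √(0.006292/0.005455), a rise of about 7%. At DE 1.84 it is √(0.008385/0.005455), a rise of 24%.

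**4. Type I error by simulation, 46 v 137.** The naive columns use a z-test with no clustering term on a 10% binary outcome, with groups of 4 to 8. The last column fits the case-manager intercept by REML to a continuous outcome, with three case managers, groups of 6 and everyone attending (4,000 trials per setting).

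| ρ | Naive, all attend | Naive, half attend | Planned case-manager model |
|---|---|---|---|
| 0 | 5.1% | – | 3.7–4.1% |
| 0.01 | 5.3–5.7% | 5.3–5.4% | 4.1–4.8% |
| 0.05 | 6.2–7.8% | 5.6–6.4% | 5.7–5.9% |
| 0.10 | 7.5–10.5% | – | 6.5–7.0% |

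The naive test on a continuous outcome reaches 11.0% at ρ = 0.10 with groups of 8. In the planned model the case-manager variance was estimated as zero in 48–63% of trials with session clustering, so the protection it gives is erratic.

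**The case against.** The strongest reply is that nothing in the document shows a positive session ICC. The only ICC it states is 0.01, and at that value the effect on sample size is under 2%. The session lasts two days within a package of individual case management and a six-week individual placement, which argues for a small ICC on employment at 12 months. Under intention-to-treat those who decline belong to no session, and {14} itself foresees that many may decline. Case managers are trained with a toolkit that also serves for conducting the sessions ({11a}), so sessions may be partly nested in case manager and the intercept would then absorb part of the session variance. All of this stands. It limits the size of the problem but does not remove the omission.

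Several stronger readings are tempting and are not supported:

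- **That the standard errors are too small as a matter of fact.** This needs a session ICC above zero beyond case manager, which the document neither gives nor implies.
- **That the type I error is about 11%.** That figure belongs to a naive test with everyone attending, groups of 8 and an ICC of 0.10. It is not the planned model.
- **That power falls from 79% to 71%.** Those figures come from an unpooled standard error, √(0.21/46 + 0.09/137) = 0.0723, against 0.0798 with a design effect of 1.25. The pooled-null formula without continuity correction gives 87% and 82% for the same case. Absolute power depends on the formula, so it should be judged with the one that produced 176.
- **That every model is affected in this way.** The harms comparison has no clustering term at all ("Adjusted analyses will not be performed for any harm data"), and the clustering structure of the complier and time-to-return analyses is not stated.

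**Conclusion.** The point holds in conditional form. The protocol describes group delivery and fixes a clustering structure that leaves it out, in both the sample size and the primary and secondary outcome models. If outcomes correlate within session groups beyond the case-manager effect, intervention-arm standard errors may be too small.

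The effect is negligible at the plan's ICC of 0.01. It is modest at assumed ICCs of 0.05 to 0.10, with a type I error of about 6 to 7% under the planned model in the setting simulated. By the plan's own formula the target of 80% power has no slack, so any positive session term takes it somewhat lower: about 76% at an ICC of 0.05 with groups of 5. The fall to 66% needs both an ICC of 0.10 and groups of 8.

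These figures assume that everyone offered the intervention attends and that session variation adds to case-manager variation. Both assumptions push the effect upwards.

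**What to change.** 1. **Record the session group** for each attender at delivery. It may be hard to reconstruct later.
2. **In {20a}, prespecify an analysis of the primary and secondary outcomes that keeps the allowance for case manager and also allows for session group**, at least as a sensitivity analysis against which the conclusion is checked. One option is cluster-robust standard errors with a small-sample correction, treating each cohort-only participant and each non-attender as their own cluster. This leaves the definition of the intention-to-treat estimate unchanged. In simulation a session-clustered variance held the error at about 3–7% where the naive test reached 11%.
3. **Say how the two levels are combined.** Standard errors clustered by session alone treat sessions that share a case manager as independent, and so lose the clustering the plan already covers. A variance clustered on both, or a session effect nested in or crossed with case manager, are candidates. With two to four case managers, that component will be poorly estimated under any choice, and the text should acknowledge this.
4. **In {14}, state the assumed group size and session ICC**, with the resulting design effect and power, computed with the formula that gives 176.

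The cost is one recorded variable, one prespecified analysis, slightly wider intervals and a somewhat less favourable power statement. No extra participants are needed for the analysis change.
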